#### Secondary outcomes

2.7.2

The secondary outcomes include the following 3 items: 

(1)Visual Analog Score (VAS): VAS will be used to assess the patients’ pain level: Some patients still have pain after surgery, and VAS will be used to evaluate the improvement of pain after oral Qishe pill/Methycobal.^[15]^(2)Neck Disability Index: Neck Disability Index will be used to assess the patients’ ability to live and work; the higher the value, the more severe the dysfunction.^[16]^(3)Increased Signal Intensity: CSM usually has increased signal intensity on MRI, and changes in spinal cord signals will be observed before and after treatment.^[17,18]^(4)Maximum Spinal Cord Compression (Fig. 2): Spinal sagittal diameters (DI) of the most severely compressed segments and the spinal sagittal diameters (DA, DB) of the uncompressed segments at the upper and lower segments will be measured at the median sagittal position of T2 weighted image (T2WI). The formula is

**Figure 2 F2:**
[figure not shown]
Measurement of percentage of median sagittal spinal cord compression in T2WI. T2WI = T2 weighted image.

(1)Compression Ratio (Fig. 3): compression ratio is the ratio of anteroposterior (AP) to laterlateral (LL). AP is the anterior and posterior diameter of the spinal cord at the level of the most severe spinal cord compression on the horizontal axis of T2WI, while LL is the left and right diameter.(2)Transverse Area (Fig. 4): The cross-sectional area of the most severely compressed spinal cord on T2WI will be measured.

**Figure 3 F3:**
[figure not shown]
Measurement methods of anterior and posterior AP and lateral LL of T2WI compressed spinal cord. AP = Anteroposterior, LLT2WI = T2 weighted image.

**Figure 4 F4:**
[figure not shown]
Measurement of the cross-sectional area of the spinal cord at the horizontal axis of T2WI. TA = transverse area, T2WI = T2 weighted image.

### Safety assessments

2.8

Qishe pill has been widely used in clinical practice, and has been found to be safe in clinical trials. Patients will be closely monitored for adverse reactions during this trial. In addition, laboratory tests will be performed at the beginning and end of the trial, including blood, urine, fecal, kidney, and liver function tests. If adverse events are reported, we will provide appropriate treatment to participants immediately.

### Participant timeline

2.9

The study will be followed for 96 weeks, from December 30, 2019 to December 30, 2021. Recruitment will start in December 30, 2019 and December 30, 2020. The recruitment process is shown in Figure 1, and the schedule is shown in Table 1.

**Table 1 T1:**
[figure not shown]
Schedule of enrollment and assessments.

### Data collection and monitoring

2.10

The duration of the intervention will be 12 weeks, and follow-up will be 36 weeks. Study visits will take place at baseline and at 4, 12, 24, and 48 weeks. Every patient will be asked to visit within 3 days of the given time point. Longhua Hospital affiliated with Shanghai University of Traditional Chinese Medicine (http://www.longhua.net/ywsy/gzlc/287.jhtml) will be responsible for quality control and training for investigators.

Epidata (version 3.0) will be used to restrict data values. Two trained investigators will enter and compare the data independently to rule out the differences.

### Quality control

2.11

All staff in the clinical study will be relatively fixed and receive unified training before the clinical trial starts, so that all investigators have a good understanding of the clinical trial protocol. All investigators will be familiar with the recording method of the case observation table and judgment standard, and will be able to teach the recording method to patients. All of the cases will be filled according to the design requirements of the “Case Record Form”. Drop-outs and withdrawals (and the reasons) from the study will be fully documented. and 2 inspectors will be appointed to supervise and inspect the research process.

### Statistical analysis

2.12

Statistical analysis includes statistical description and statistical inference. The statistical description of quantitative index includes mean, standard deviation, median, minimum, and maximum. The qualitative index is described by frequency table and composition ratio. Statistical inference includes interval estimation and hypothesis testing.

All statistical analysis will be conducted by Statistical Packages of Social Sciences software (version 22.0). By the bilateral test, *P* < .05 will be considered to be statistically significant. The mean ± standard deviation will be used for the description of continuous variables. Continuous variables following the normal distribution will be analyzed by Student *t*-test. The non-normally distributed data will be tested using the rank sum test. The non-grade data in the counting data will be tested with the 2 test or the non-parametric test. The grade data will be checked by Ridit.

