### Sample size calculation

2.4

On the basis of the comparison treatment, we calculated the sample size of the 2 groups (Qishe pill versus Methycobal), which will be randomly distributed in an equal manner. Since Japanese Orthopaedic Association (JOA) scores can include sensory and motor function of the limbs and bladder, we chose JOA scores to calculate the sample size with an estimated correlation coefficient of the measurements of ρ=0.8 and with an alpha = 0.05. The JOA score was 13.68 ± 1.83 at the 6-month follow-up after oral administration of Methycobal, and 15.65 ± 1.61 at the 6-month follow-up after oral administration of traditional Chinese medicine for promoting blood circulation and removing blood stasis, so the calculated sample size of each group is 132. Considering a 20% loss to follow-up, the total sample size needed to detect this difference at a 5% level of significance with a power of 90% is 330 patients.

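### The t-test or rank sum test named for JOA, chosen by observed distribution, leaves baseline adjustment and the correlation across visits unused, although planning assumes a correlation of 0.8

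*Protocol article*

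**What the plan says.** Section 2.12 (Statistical analysis) fixes the test for continuous outcomes: "Continuous variables following the normal distribution will be analyzed by Student" t-test, and otherwise "The non-normally distributed data will be tested using the rank sum test". Tests are two-sided at 0.05. No covariate and no repeated-measures term is named.

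The design around that rule is longitudinal. Section 2.10 states "Study visits will take place at baseline and at 4, 12, 24, and 48 weeks". The abstract defines the primary outcome as JOA from baseline to each of the four post-surgery visits, and section 2.7.1 adds a comparison of the JOA improvement rate. Section 2.4 sizes the trial on JOA "with an estimated correlation coefficient of the measurements of ρ=0.8" and describes JOA by means and standard deviations, so the plan itself treats JOA as continuous. The same section allows for 20% loss to follow-up.

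**The concern.** Section 2.12 makes a positive choice of method, and that choice does not fit the design. A two-sample t-test or rank sum test compares two sets of single values. It cannot adjust for baseline JOA as a covariate, and it cannot draw on a patient's other visits. Section 2.4 nevertheless carries a correlation between measurements into the planning, where it has a role only if the analysis uses repeated measurements in some way.

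The choice of test also depends on the observed distribution. The t-test addresses a difference in means and the rank sum test a shift in ranks, so the quantity reported could differ from one visit to the next. With 132 evaluable patients per group, a t-test on means is robust to moderate non-normality, so the switch gains little.

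At stake are wider intervals than the data allow, chance baseline imbalance that is not adjusted for as well as it could be, and an effect measure that is not settled before the data are seen.

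**Working it through.** **Inputs.** Section 2.4: means 13.68 and 15.65; SDs 1.83 and 1.61; ρ = 0.8; two-sided 0.05; 90% power; 132 evaluable per group; 20% loss. Section 2.10: four follow-up visits. Assumed here: equal variance at baseline and follow-up, and ρ between baseline and follow-up, with 0.5 and 0.3 as alternatives.

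**The plan's own figure.** Difference = 15.65 − 13.68 = 1.97. Pooled SD = √((1.83² + 1.61²)/2) = 1.7235. n per group = 2 × ((1.960 + 1.282) × 1.7235 / 1.97)² = 16.1, so 17, not 132. Using ρ = 0.8 lowers this to about 6 (ANCOVA) or 7 (change score). The dropout step does reproduce: 132/0.8 = 165 per group, 330 in total. The failure of 132 to reproduce is a separate matter; 132 is taken as given below.

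**Variance of the treatment difference**, relative to a t-test on raw follow-up scores:

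- change-score t-test: 2(1 − ρ)
- ANCOVA: 1 − ρ²
- ANCOVA relative to change: (1 − ρ²) / (2(1 − ρ)) = (1 + ρ)/2

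**Detectable difference** at 90% power with 132 per group, raw scores: 3.242 × 1.7235 × √(2/132) = 0.69 JOA points. The other detectable differences multiply this by the square root of the variance ratio.

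| ρ | ANCOVA / raw | change / raw | ANCOVA / change | Detectable: raw | change | ANCOVA |
|---|---|---|---|---|---|---|
| 0.8 | 0.36 | 0.40 | 0.90 | 0.69 | 0.43 | 0.41 |
| 0.5 | 0.75 | 1.00 | 0.75 | 0.69 | 0.69 | 0.60 |
| 0.3 | 0.91 | 1.40 | 0.65 | 0.69 | 0.81 | 0.66 |

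Both ANCOVA ratios are at most 1 for any ρ between 0 and 1, apart from one degree of freedom, which is negligible at this size. Which simple test is the poorer one depends on ρ: raw scores above 0.5, change scores below it. The improvement rate is not in the table because the article gives no variance for it.

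**If ρ = 0.8 is the correlation between follow-up visits instead**, averaging the four visits without baseline has variance (1 + 3 × 0.8)/4 = 0.85 of a single visit, a modest gain.

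**Power at the stated difference.** With a difference of 1.97, SD 1.7235 and 132 per group, the raw-score t-test has power above 99.9%. Even the largest detectable difference in the table, 0.81, is well below 1.97.

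**The case against.** A t-test in a randomised trial is valid, and several stronger criticisms that a reader might infer are not supported.

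- *That baseline JOA is ignored.* The abstract's outcome wording and the improvement rate in section 2.7.1 both suggest that baseline may enter through the outcome variable. If change is tested and ρ is 0.8, ANCOVA saves only a further 10% of variance. What can be said is that baseline is not used as a covariate.
- *That power is seriously impaired.* For a difference of 0.5 points at ρ = 0.8, power is 65% with raw scores and 97% with adjustment. But 0.5 points is an illustrative value found nowhere in the article, and with a change score the comparison is 96% against 97%.
- *That the plan expects exactly the precision it discards.* Section 2.4 does not say which measurements the 0.8 relates.
- *That 66 patients (20% of 330) will be excluded.* No analysis set or missing-data rule is stated, the 20% is not tied to a visit, and such rules may sit in a document not shown. Enrolment already allows for the loss. The supportable statement is conditional: a visit-wise two-sample test without imputation uses only patients seen at that visit.
- *That leaving out a hospital term is an error.* Section 2.6 describes no stratification, so its absence contradicts nothing.

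These objections limit the size of the point. They do not remove it: section 2.12 names its tests affirmatively, so this is more than detail left for later, and neither test uses the longitudinal structure under any reading of ρ.

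**Conclusion.** The point holds as one of efficiency and prespecification. Section 2.12 lets the data choose between two simple tests, neither of which adjusts for baseline or uses the repeated visits. Baseline adjustment would have 0.36 to 0.91 of the variance of a raw-score t-test, and 0.65 to 0.90 of that of a change-score t-test, for correlations between 0.3 and 0.8. These ranges assume that ρ is the baseline-to-follow-up correlation and that variances are equal over time. The article settles neither the meaning of ρ nor the variable tested, so the gain cannot be narrowed further than modest to large. On the plan's own 1.97-point difference the trial's conclusion is not endangered by the lost precision. The change should be made because it is nearly free, not because the stated analysis would be invalid.

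**What to change.** In section 2.12, name one primary JOA analysis: a baseline-adjusted linear model, preferably a mixed model for repeated measures over weeks 4, 12, 24 and 48, with baseline JOA, treatment, visit and treatment-by-visit, in all randomised patients as allocated. Such a model also keeps the earlier visits of patients lost later, on the assumption that data are missing at random.

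Report the treatment difference with its 95% confidence interval at one visit that the sponsor names in advance. Week 24 is one option, since it matches the 6-month data behind the sample size; the choice is the sponsor's. Drop the normality-driven switch and keep the rank sum test as a sensitivity analysis. State in section 2.4 which correlation the 0.8 is. Terms for hospital and surgical approach are optional.

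The cost is a change of wording, a little more programming and the assumptions of the model. No new data are needed.

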## Discussion

3

Patients with CSM have a high rate of surgery, and some patients have obvious residual symptoms.^[19]^ In the absence of established guidelines, treatment should center around relief of patient symptoms. Treatment modalities include bed rest, medications, physical exercise, thermal therapy, and others.^[20,21]^ Therefore, it is important to explore new treatment options to alleviate postoperative symptoms and improve the quality of life of patients. To the best of our knowledge, this is the first randomized controlled clinical trial to investigate the efficacy of the Qishe pill in the treatment of postoperative residual symptoms of CSM.

The Qishe pill is a combination of eight herbal ingredients and has been widely used in the clinical setting, and can significantly reduce the stiffness and numbness of the neck and shoulder. It is recommended for treating a variety of ailments, including neck pain, radiating pain, limb stiffness and numbness, weakness, fatigue, and other symptoms. Related studies have proven that astragalus and chuanxiong have the effects of nourishing qi, generating blood, and improving circulation.^[22,23]^ However, there remains a lack of evidence for the residual neck and shoulder pain and numbness of CSM. Therefore, this clinical study will be conducted to explore the efficacy and safety of the Qishe pill to provide a new therapeutic scheme for clinical improvement of postoperative residual symptoms of CSM.
